## Abstract

**Background:**

Obesity-related diseases have a profound economic impact on health care systems. Laser acupuncture has been shown to have beneficial effects on obesity. However, to our knowledge, those trials were either non-randomized, non-blinded or included low-calorie diet control. We have, therefore, designed a patient-assessor-blinded, randomized, sham-controlled crossover trial to investigate the significance of laser acupuncture on obesity.

**Methods/Design:**

104 subjects above 20 years of age with a body mass index (BMI) of over 25 kg/m^2^ will be divided into 2 groups: experimental and control. Each subject will receive the treatment relevant to their group 3 times a week for 8 weeks. After 8 weeks of treatment the subject will enter a 2-week washout period, after which the subjects will switch groups. Measurements will include BMI, body fat percentage, waist-to-hip ratio (WHR), waist circumference, hip circumference, skinfold thickness, thigh circumference, body fat, blood pressure, heart rate, hunger and the 36-item Short-Form Health Survey (SF-36).

**Discussion:**

The results of this study will provide the basis for future large-scale multicenter trials investigating the effects of laser acupuncture on obesity.

**Trial registration:**

ClinicalTrials.gov Identifier: NCT02167308; registration date: 14 June 2014.

**Electronic supplementary material:**

The online version of this article (doi:10.1186/s13063-015-0748-4) contains supplementary material, which is available to authorized users.

## Background

The number of obese people around the world has been increasing rapidly. It has been estimated that over 10% of the world’s adult population are obese [1]. Obesity is associated with increased risk of coronary heart disease, type II diabetes, stroke, osteoarthritis and certain types of cancer. These deleterious conditions are detrimental to individuals’ quality of life, and places emotional and financial burden on the individual, their families and society as a whole [2]. Much more needs to be done to improve treatments for obesity.

Current methods to treat obesity include dietary intervention, lifestyle intervention, drug intervention or bariatric surgery. Among these, acupuncture, in a comprehensive program for weight loss, has been increasing in popularity. However, previous systematic reviews assessing the effects of acupuncture on obesity discovered promising but inconclusive results. The low-quality methodology used in those trials further reduced the strength of those conclusions [3, 4]. In addition, the lack of safety procedures used in traditional manual acupuncture could lead to adverse events such as retroperitoneal abscess, rapid dermal spread of breast cancer, pneumothorax, cardiac tamponade, viral hepatitis and granuloma [5].

In comparison with traditional manual acupuncture, laser acupuncture therapy has several advantages. These advantages include ease of application, precision in dose measurement, painlessness and non-invasiveness. It is a quick and safe therapy with low cost and no risk of infection. As laser acupuncture does not produce local sensation, double-blind randomized controlled studies are also much easier to perform.

Laser acupuncture has been widely used in medical fields for over 30 years. Clinical research on the efficacy of laser acupuncture has also increased [6, 7]. Several studies have shown that laser acupuncture could be an effective treatment of obesity [8, 9]. Low-level laser therapy as a non-invasive approach for body contouring and spot fat reduction has also been reported [10, 11]. However, there are several experimental limitations that have to be considered. For instance, absence of placebo (sham) control, combination with low-calorie diet and lack of sufficient comparative parameters have been questioned [12]. For these reasons, we decided to conduct a patient-assessor-blinded, randomized, sham-controlled crossover pilot trial to investigate the effects of laser acupuncture with Gallium Aluminum Arsenide (GaAlAs) laser irradiation on weight loss, fat reduction, body contouring and quality of life in people suffering from obesity.

## Methods/Design

### Aim of the study

The aim of this study is to assess the effectiveness of laser acupuncture in the treatment of obesity. We will evaluate whether laser acupuncture changes body mass index (BMI), body fat percentage, waist-to-hip ratio (WHR), waist circumference, hip circumference, thigh circumference, body fat, blood pressure, heart rate, hunger and quality of life. All adverse events will also be assessed.

### Study design

This study proposes a patient-assessor-blinded, randomized, sham-controlled crossover trial with a 2-week washout period between each crossover phase. The trials will be conducted at the Chiayi Chang Gung Memorial Hospital. This study will adhere to the recommendations of the Consolidated Standards of Reporting Trials (CONSORT) [13] to allow for greater completeness, transparency and accuracy of reporting. The protocol for this study has been registered in the Clinical Trials register (ClinicalTrials.gov Identifier: NCT02167308).

Subjects who voluntarily sign a consent form will undergo the trial according to the study design. When a subject is determined to be fit for participation based on inclusion and exclusion criteria, the subject will be randomly assigned to 1 of 2 groups in a ratio of 1:1. One group is the true laser experimental group and the other is the sham laser control group. Each group will receive their treatment 3 times a week for 8 weeks. After 8 weeks of treatment and a 2-week washout period, the control group will switch to the experimental group while the experimental group will switch to the control group. The subjects then undergo the treatment of their new group for another 8 weeks (Fig. 1).

**Fig. 1 Fig1:**
[figure not shown]
Flowchart of the study design

Treatment and assessment will be performed independently and the practitioners will not be involved in assessing the outcome of the treatment. The subjects, the outcome assessors and the statistician performing the data analyses will be blinded to the treatment allocation throughout the study.

### Sample size

This study is a pilot study for evaluating the efficacy of actual laser acupuncture compared to sham laser acupuncture, and to evaluate the feasibility of large clinical trials. In the hopes of decreasing the subject drop-out rate, the trial is designed to only last 8 weeks. Assuming a drop-out rate of 10%, the desired sample size for this pilot study is 104 subjects, with 52 in each group. Based on the *a priori* calculation in G*Power 3.1.3 [14] it was determined that a minimum total sample size of 92 would be needed in a repeated measures between factors design to show a significant difference (effect size = 0.25; α = 0.05; 1 – β = 0.8; number of measurements = 8; correlation among repeated measures = 0.2).

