### Statistical analysis

Statistical analysis will be performed by using the software program Statistical Package for the Social Sciences (SPSS 15.0, Chicago, IL, USA). Participants’ demographic information and levels of major measured variables were analyzed by descriptive statistics. Means and standard deviations of the clinical indices will be calculated, after which the evaluation between the two groups will be compared using a Student’s *t*-test. The difference of evaluation scores before and after each examination point will be analyzed using paired *t*-tests. The repeated measures analysis of variance (ANOVA) will be used to analyze longitudinal and repeated measured data for the clinical indices across the 8 data collection points (treatments for 16 weeks, followed-up evaluation biweekly). A value of *P* < 0.05 will be regarded as statistically significant for the above statistical analyses.

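### The 10% drop-out allowance is supported by a trial length of 8 weeks, but the crossover keeps each subject for 18 weeks plus follow-up, and the period the 10% covers is not stated

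*Protocol article*

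**What the plan says.** The Sample size section gives one reason to expect few losses: "In the hopes of decreasing the subject drop-out rate, the trial is designed to only last 8 weeks". The next sentence reads "Assuming a drop-out rate of 10%, the desired sample size for this pilot study is 104 subjects", split 52 and 52. The section then reports that "a minimum total sample size of 92 would be needed in a repeated measures between factors design", with inputs that include "effect size = 0.25", "number of measurements = 8" and "correlation among repeated measures = 0.2", α = 0.05 and power 0.8.

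The Study design section describes a longer trial. Each subject has 8 weeks of treatment at 3 sessions a week and a 2-week washout, and then: "The subjects then undergo the treatment of their new group for another 8 weeks". The Statistical analysis section speaks of 16 weeks of treatment. The Outcome assessment and Follow-up sections add an assessment 2 months after the last treatment.

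For the longitudinal data, the Statistical analysis section names repeated measures ANOVA, run in SPSS 15.0, which "will be used to analyze longitudinal and repeated measured data for the clinical indices across the 8 data collection points".

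**The concern.** The 8 weeks in the Sample size section is the length of one treatment period, not of the trial. It is the only reason given beside the 10% figure, so part of the basis for 104 is wrong as written. The article gives no source for the 10% and does not say what time it covers.

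This matters because the margin is thin. At exactly 10% loss, 93.6 subjects are expected against a stated minimum of 92. A within-subject crossover contrast also needs data from both periods, so losses in the washout and the second period count in full.

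The planned longitudinal method bears on the same number. Classical repeated measures ANOVA uses only subjects with a value at every time point, so a subject who stays in the trial but misses one biweekly visit would leave that analysis.

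**Working it through.** **Duration.** From the Study design section: 8 + 2 + 8 = 18 weeks from first to last treatment, and 3 × 8 × 2 = 48 sessions. Adding the 2-month follow-up, taken as about 8 weeks, gives about 26 weeks. The Sample size section says 8.

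**The plan's own drop-out step.** 92 / (1 − 0.10) = 102.2, which rounds up to 103, or to 104 for equal groups. This step reproduces.

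**Margin.** 104 × 0.90 = 93.6 expected completers. The drop-out at which 92 are just reached is 1 − 92/104 = 11.5%.

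**Completers under each reading of the 10%.** The chance of at least 92 of 104 is binomial, with losses independent between subjects.

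| Reading of the 10% | Proportion completing | Expected completers | P(at least 92) |
|---|---|---|---|
| Whole trial | 0.90 | 93.6 | 0.76 |
| Each 8-week treatment period (assumption) | 0.9² = 0.81 | 84.2 | 0.03 |
| Per 8 weeks at a constant rate over 18 weeks (assumption) | 0.9^(18/8) = 0.789 | 82.1 | 0.008 |

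To keep 92 completers under the second and third readings, 92/0.81 = 113.6 (114) and 92/0.789 = 116.6 (117) subjects would have to be enrolled.

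**Missed visits.** The expected number with all 8 values is 93.6 × (1 − q)^8, where q is the chance of missing any one visit, independent between visits. The article gives no q, so these values are illustrative only: 1% gives 86.4, 2% gives 79.6 and 3% gives 73.4. The expected number falls below 92 once q exceeds 1 − (92/93.6)^(1/8) = 0.2%.

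**Is 92 the right benchmark?** The stated inputs were put into the between-factors repeated measures F test with 2 groups, reading the effect size as Cohen's f (an assumption, and the G*Power convention for ANOVA). The noncentrality is λ = f² × N × m / [1 + (m − 1)ρ], with 1 and N − 2 degrees of freedom. With f = 0.25, m = 8 and ρ = 0.2, λ = 0.0625 × 8N / 2.4 = 0.2083N.

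- N = 40: λ = 8.33, power 0.803. N = 39 gives 0.793, so 40 is the minimum.
- N = 92: λ = 19.17, power 0.991.
- N = 84, 82 and 73: power 0.985, 0.983 and 0.970.

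The stated 92 therefore does not follow from the stated inputs.

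**The case against.** The strongest reply is that the article never calls the 10% a rate per 8 weeks. It stands beside the enrolment total for the whole trial. Read as a whole-trial rate, it makes 92 completers likely, and the drop-out arithmetic is correct. This stands. A reader might infer that 92 analysable subjects are unlikely, but that needs a per-period rate, or a missed-visit rate, that the document does not give.

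A second reply is that whole-case deletion is a software default and not something the article states. Missing-data handling may be set out in a full protocol or analysis plan that is not shown. The t-tests and paired t-tests in the same section do not need all 8 values either. This also stands, so the absence of a missing-data rule is not a finding here, and the missed-visit figures show sensitivity only. What remains is that the method the article names discards incomplete subjects in its usual form.

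A third reply is that no loss of power follows. A reader might take fewer than 92 completers to mean power below 80%. On the stated inputs it does not: power is 0.97 or more for every number of subjects from 73 to 84. This reply offers limited comfort, because the calculation is for a between-group comparison and not for the crossover contrast, and its 92 does not reproduce.

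None of these replies touches the contradiction over duration.

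**Conclusion.** The point holds as a contradiction in the document. The drop-out allowance is supported by an 8-week trial, while the design keeps each subject for 18 weeks and 48 sessions plus a follow-up assessment. This needs no assumption.

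The effect on the number of completers depends on what the 10% means. Over the whole trial, about 94 complete and the chance of at least 92 is 76%. Per 8 weeks, about 82 to 84 complete and the chance is about 1 to 3%. The document does not settle which is meant, so a shortfall is possible but not shown. It does not show an underpowered trial either: the stated inputs give 40, and power for the actual crossover analysis has not been stated. The failure of 92 to reproduce is a separate matter that the same revision should address.

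**What to change.** 1. In the Sample size section, replace the 8-week duration with the length the design implies: 18 weeks from first to last treatment, plus the assessment 2 months later.
2. State the period the 10% covers and the basis for it, and give the expected completers over both periods: about 94 if it is a whole-trial rate, about 82 to 84 if it is per 8 weeks.
3. Give the power for that number under the actual crossover analysis, and reconcile the stated inputs with the 92.
4. For the longitudinal analysis, replace repeated measures ANOVA with a linear mixed model fitted by REML to all available visits, with treatment, period and sequence as factors. Subjects with only first-period or partial data then still contribute.

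The cost is wording, a little more analysis work and possibly a less favourable stated number of completers. No patients are added.

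### The stated minimum of 92 does not follow from its own inputs, which give 40, and the calculation powers a sequence comparison, not laser versus sham

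*Protocol article*

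**What the plan says.** The Sample size section of the protocol article says that the pilot evaluates the efficacy of real against sham laser acupuncture. It reports a G*Power 3.1.3 result that "a minimum total sample size of 92 would be needed in a repeated measures between factors design to show a significant difference". The inputs listed are "effect size = 0.25", alpha 0.05, power 0.8, and "number of measurements = 8; correlation among repeated measures = 0.2". The 92 is raised to 104, 52 per group, for 10% drop-out. The number of groups is not among the listed inputs.

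The Study design section describes a "randomized, sham-controlled crossover trial with a 2-week washout period between each crossover phase". It says that "the subject will be randomly assigned to 1 of 2 groups in a ratio of 1:1" and that each group then switches to the other treatment for a further 8 weeks. The Statistical analysis section places the 8 data collection points over 16 weeks of treatment, assessed every two weeks.

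**The concern.** There are two separate problems.

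First, the section names the software, the test and nearly all the inputs, so its result can be checked, and it does not reproduce. The stated figure is 2.3 times what the inputs give (92/40). At least one published figure is therefore wrong.

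Second, the section justifies the trial as a comparison of laser with sham, but the named test compares the randomised groups averaged over all measurements. In a crossover where every subject receives both treatments, that is not the treatment comparison. The 80% would then describe a question the trial does not set out to answer, and no power would be stated for the one it does.

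**Working it through.** **Inputs.** From Sample size: f = 0.25, alpha = 0.05, power = 0.80, m = 8 measurements, rho = 0.2, and the between-factors test ("would be needed in a repeated measures between factors design"). From Study design: k = 2 groups, allocated 1:1.

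**Reproducing the plan's figure.** For the between-factors test in repeated-measures ANOVA, the noncentrality parameter is

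lambda = f² × N × m / (1 + (m − 1) × rho), with k − 1 and N − k degrees of freedom.

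Here 1 + 7 × 0.2 = 2.4, so lambda = 0.0625 × N × 8 / 2.4 = 0.2083 N, with 1 and N − 2 degrees of freedom.

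| N | lambda | Power |
|---|---|---|
| 38 | 7.92 | 0.782 |
| 40 | 8.33 | 0.803 |
| 92 | 19.17 | 0.991 |

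The smallest balanced total with at least 80% power is 40. As a cross-check, the normal approximation for the mean of 8 measures (standardised difference 2f = 0.5, SD of the mean √(2.4/8)) gives 38.

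**Can 92 be recovered?**
- Other repeated-measures tests, same inputs: the within-factors test gives 24 (one group) or 26 (two groups), and the within-between interaction gives 26.
- Stricter alpha: 0.025 gives 50 and 0.01 gives 60.
- Number of measurements from 2 to 11: the total falls from 78 to 38 and is never 92.
- Number of groups, the one unlisted input: ten groups would give 90, but the design has two.
- A within-factors test with the nonsphericity correction at its lower bound of 1/7 gives 90, but that is not the named test.
- Changing one stated input does reach it: power 0.99 gives exactly 92, and a correlation of 0.66 or 0.67 gives 92. At rho = 0.66, lambda = 0.0625 × 92 × 8 / (1 + 7 × 0.66) = 46/5.62 = 8.19, and power is 0.81. An f of 0.16 gives 94 and 0.165 gives 90.

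**Drop-out step.** 92/0.9 = 102.2, which rounds up to 103, or 104 for equal groups. This step is consistent with 92 and does not explain the discrepancy.

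**What the between factor tests.** Sixteen weeks of treatment assessed every two weeks gives 16/2 = 8 points, four in each 8-week period. Let mu be the overall mean, p1 and p2 the period effects, and tau the laser-minus-sham effect, equal in both periods.
- Laser then sham, averaged over both periods: mu + (p1 + p2)/2 + tau/2.
- Sham then laser, averaged over both periods: mu + (p1 + p2)/2 + tau/2.

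The difference between the groups is zero whatever the value of tau. What remains in the between-group comparison is sequence or carryover. The treatment effect lies within subjects (laser period minus sham period), or between groups in period one only.

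**What 92 completers can detect at 80% power, two-sided alpha 0.05.**
- Within-subject contrast: (1.960 + 0.842)/√92 = 2.802/9.592 = 0.292. With the t distribution this is 0.295, about 0.30 SD of the within-subject difference.
- Period one only, 46 versus 46: 2.802 × √(2/46) = 0.584. With the t distribution this is about 0.59 SD of the outcome.

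**The case against.** The strongest reply is that nothing in the conduct of the trial changes. The error is on the safe side for the named test: both 92 and 104 exceed 40. The trial is described as a pilot that also assesses feasibility, and 92 completers can detect a modest within-subject effect. This stands, and it is why the point is a correction to make and not a threat to the trial.

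A second reply is that an input may simply have been mistyped. This also stands. Changing one stated input recovers 92, and the article cannot show whether an input or the 92 is at fault. A reader might infer that the trial needed only 40 subjects. That goes too far: 40 is what the printed inputs give for the named test, and that test does not address the treatment effect.

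A reader might also infer the opposite, that 92 is too few, by arguing that repeated BMI values in one person correlate far more than 0.2 and that a higher correlation lowers power for a between factor. The documents do not support that either. They give no correlation for BMI, and the primary outcome is change from baseline, which need not share the correlation of BMI itself. The argument also relies on the between-factors formula, which is not the treatment contrast. For the within-subject contrast, with the total SD and raw difference held fixed, a higher correlation raises power.

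Nor is it a fault that the effect size is given without BMI units. Cohen's f is the usual G*Power input, and an article commonly leaves the SD and raw difference to the full protocol.

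Finally, the Sample size section speaks of a trial lasting only 8 weeks, which could suggest a parallel-group calculation. But biweekly assessment over 8 weeks cannot supply 8 measurements, and the Statistical analysis section ties the 8 points to 16 weeks.

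**Conclusion.** Wrong as written; should be fixed. The stated inputs with two groups give a minimum of 40 (power 0.803), and 92 has power 0.991 under them. No ordinary variant that keeps those inputs returns 92. The mismatch is conservative for the named test, and which figure is wrong cannot be settled from the article.

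The named between-factors test over both periods is a comparison of sequences, so no power is stated for laser versus sham. This does not show that the trial is underpowered. The size may well be adequate, but the published calculation does not demonstrate it.

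The arithmetic rests on two groups, as in the Study design section, and on reading the effect size as Cohen's f, as G*Power does for ANOVA. The sequence argument rests on the 8 measurements in the calculation being the 8 points of the Statistical analysis section.

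**What to change.** Keep 104 enrolled. In the Sample size section:
1. Reconcile the printed inputs with the 92, by correcting whichever is wrong or withdrawing the calculation.
2. Replace it with one for the contrast that will test laser versus sham: the within-subject treatment contrast, or a first-period between-group contrast if that is the intended analysis.
3. Restate the detectable effect for that contrast. For 92 completers at 80% power it is about 0.30 SD of the within-subject difference, or about 0.59 SD for 46 versus 46 in period one.

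The cost is rewriting one paragraph, with no change to enrolment.

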### Ethics

This research protocol adheres to the principles of the *Declaration of Helsinki* and has been approved by the institutional review boards of the Chang Gung Memorial Hospital (103-1403A3). Informed consent will be obtained from each participant before any treatment is given. All subjects will have the right to withdraw from the study at any time.

### Inclusion criteria

Individuals are eligible if they are above 20 years of age and have a BMI over 25 kg/m^2^. BMI cutoffs were adopted from a proposed classification of weight by BMI in adult Asians, including the Obese I (BMI: 25 to 29.9 kg/m^2^) and Obese II (BMI ≥ 30 kg/m^2^) categories [15].

